### Safety evaluation

To determine safety, lab test results will be compared to the baseline to identify any clinical changes. AE that occurred during the study period will be listed and thoroughly explained. All SAE will be thoroughly described. AE will be gathered through patient-reported symptoms and investigator-made observations. The frequency of AE associated with and unrelated to the intervention will be recorded and presented as descriptive statistics. If necessary, additional statistical analysis will be performed based on the nature of the variables and the purpose of the evaluation.

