# DJ-E-### [DJ: Daejeon University Daejeon Oriental Medicine Hospital, E: Enrollment, ###: Serial number (001, 002, 003,…)] (e.g., DJ-E-088: Daejeon Korean Medicine Hospital of Daejeon University’s 88th enrolled subject).

### Blinding

The test staff (i.e., investigator) will be divided into intervention staff and evaluation staff. The intervention staff will perform MARS-PD intervention, provide medical consultations to test subjects, and record case report forms (CRFs). Due to the nature of the intervention method used in this clinical trial, blinding of the subjects and the intervention staff will not be possible. Only blinding of the evaluation staff and statisticians will be possible in this study. To reduce the risk of unblinding caused by electronic medical records (EMRs) and CRFs, and orders will be recorded under the name of the intervention staff, not the evaluation staff. The evaluation staff will determine the research subjects’ eligibility, obtain signed ICF from the subjects, assign screening numbers and identification codes to the subjects, and perform evaluations. The evaluation staff should not be aware of the subjects’ treatment. The clinical research coordinator (CRC) will manage the subjects’ schedules and complete the CRFs as part of the basic clinical trial work. Blinding of the CRC cannot be maintained. The outcome assessor will be blinded.

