### Efficacy evaluation

The primary outcome, the mean change in MDS-UPDRS Part III score from baseline at 8 weeks between the experimental and control groups will be assessed using an independent t-test. If there is a significant difference in the baseline between the groups, we will use an analysis of covariance. If there is a significant difference in the other baseline variables, we will employ multiple regression analysis. The MDS-UPDRS Part III scores will be assessed at each time point within the confines of a linear mixed effects model with fixed effects for treatment, time, and the interaction of treatment by time, and an unstructured covariance structure for repeated measures within each subject.

The secondary outcomes include the MDS-UPDRS, IPAQ Short Form, PSQ, PDSS, TUG results, GAITRite parameters, fNIRS measurements, number of steps per day, gut microbiome analysis results, and iris connective tissue texture and density. To evaluate the secondary outcomes, we will use analysis of covariance or multiple regression analysis with corrected baseline variables. When the baseline variable is used as a covariate, a PP analysis will be performed without processing missing values.

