### Adverse events

Adverse events (AEs) refer to any harmful and unintended signs, symptoms, or diseases that occur in test subjects who have received a clinical trial intervention and do not necessarily have a causal relationship with the relevant intervention method. Serious adverse events (SAEs) refer to any of the following AEs that occur as a result of clinical trial intervention: (1) when death or a threat to life occurs, (2) when hospitalization is required or the hospitalization period must be extended, (3) when there is permanent or serious disability or functional decline. The subject who has developed an AE must be monitored by the test staff until the symptoms have subsided and his or her condition has stabilized. If there is a request from the client, a report on the progression of the AE must be submitted.

The principal investigator (PI) must explain to the test staff, subjects, and their guardians all possible AEs that may occur and train them to report any phenomena that appear after the intervention. All SAEs that occur during the study period must be reported to the PI within 24 hours, regardless of whether they are related to the intervention or not. If an SAE occurs, the PI must inform the client (Daejeon Korean Medicine Hospital of Daejeon University) promptly and provide comprehensive details in writing within 5 days. Clinical trials must be halted until further instructions are given. All serious and unexpected AEs must be disclosed immediately to other relevant investigators, the Institutional Review Board (IRB), and the Ministry of Food and Drug Safety (MFDS) within the specified time frame: (1) within 7 days of notification to the client for death or life-threatening AE, with additional detailed information provided within 8 days of the initial report date; (2) within 15 days of notification to the client for all other serious or unexpected AE. SAE must be documented in the report, and the following information should be included in the final report, if possible: data on the occurrence of the SAE, its severity, treatment, course, and causal relationship with the intervention.

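### The safety analysis names change from baseline and judged relation to MARS-PD as its comparisons, and names no contrast between the randomised arms

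*Protocol article*

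**What the plan says.** The Safety evaluation section of the protocol article gives these analysis rules:

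- Laboratory values: "lab test results will be compared to the baseline to identify any clinical changes".
- AE listing: "AE that occurred during the study period will be listed and thoroughly explained". SAEs are also to be described in full.
- AE frequency: "The frequency of AE associated with and unrelated to the intervention will be recorded and presented as descriptive statistics".
- Anything further: "If necessary, additional statistical analysis will be performed based on the nature of the variables and the purpose of the evaluation".

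No sentence of that section mentions the two arms. Elsewhere the article does name the comparator. Under Efficacy evaluation, the primary outcome "between the experimental and control groups will be assessed using an independent t-test". Under Economic evaluation, MARS-PD is set against usual care. The title and the Abstract include safety among the trial's aims. The Discussion lists safety among the goals and then names usual care as the trial's comparator. Under Blinding, "blinding of the subjects and the intervention staff will not be possible", and the intervention staff record the case report forms.

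**The concern.** Randomisation gives this trial a control group that shares calendar time, disease course, repeat measurement and regression to the mean with the MARS-PD group. A comparison with each patient's own baseline does not use that group. Any shift between visits, whatever its cause, enters the comparison together with any effect of MARS-PD.

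Grouping AEs by judged relation has a different weakness. Usual-care patients receive no MARS-PD during the comparison, so an event associated with MARS-PD has no real counterpart in their arm. Falls, muscle pain or fatigue could become more frequent with exercise, but they also occur without it, so they can reasonably be judged unrelated one by one. An excess of such events shows only in all-cause counts compared between arms. The judgement is also made in an open trial, and events come from sources that know the allocation at least in part: "AE will be gathered through patient-reported symptoms and investigator-made observations".

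At stake is whether the trial's safety statement rests on the randomised comparison or on something weaker, when the randomised comparison is available.

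**Working it through.** The safety section contains no figure to reproduce. The check is therefore of what the named summaries can and cannot identify, followed by illustrations. All rates and drifts below are assumptions. Only the 44 patients per arm comes from the article (Abstract and Sample size).

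**1. Comparator named for each objective**

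| Objective | Section | Comparator named |
|---|---|---|
| Efficacy | Efficacy evaluation | control group |
| Cost-effectiveness | Economic evaluation | usual care |
| Safety, laboratory | Safety evaluation | patient's own baseline |
| Safety, AEs | Safety evaluation | judged relation to the intervention |

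**2. What a relatedness table shows if it is not split by arm**

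Count patients with an AE in two assumed trials:

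- Trial A: MARS-PD 18/44 (2 judged associated, 16 unrelated); control 9/44 (all unrelated).
- Trial B: MARS-PD 14/44 (2 associated, 12 unrelated); control 13/44 (all unrelated).

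Associated: 2 in both trials. Unrelated: 16 + 9 = 25 in A and 12 + 13 = 25 in B. The pooled tables are identical. The arm differences are not:

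- A: 18/44 − 9/44 = 40.9% − 20.5% = 20.5 points, Newcombe 95% CI 1.2 to 37.8.
- B: 14/44 − 13/44 = 31.8% − 29.5% = 2.3 points.

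Split by arm, the same table gives 2 + 16 = 18 against 9 in trial A, and the excess is visible. So the gap is the missing split by arm, not lost events.

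**3. What a before-after laboratory comparison shows, if it is tested**

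Suppose both arms drift by d standard deviations of change and MARS-PD has no effect. The chance that a two-sided 5% before-after test in the 44 MARS-PD patients is significant is Φ(d√44 − 1.96) + Φ(−d√44 − 1.96) (normal approximation):

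| d | d√44 | Before-after test | Between-arm test |
|---|---|---|---|
| 0.2 | 1.33 | 26% | 5% |
| 0.3 | 1.99 | 51% | 5% |
| 0.5 | 3.32 | 91% | 5% |

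In the other direction, suppose controls shift by 0.7 SD of change and MARS-PD patients stay flat. The before-after test in the MARS-PD arm flags 5%. The between-arm test has power Φ(0.7/√(2/44) − 1.96) = 91%.

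These figures show the direction of the problem only. The article names no laboratory test and gives no drift.

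**4. Precision of the arm contrast**

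Approximate 95% CI half-width for a risk difference at 44 per arm, 1.96 × √[(p₁(1 − p₁) + p₂(1 − p₂))/44]:

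- 5% against 20%: 1.96 × √(0.2075/44) = 13.5 points; power 57%.
- 10% against 30%: 1.96 × √(0.30/44) = 16.2 points; power 66%.

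This supports estimates with intervals rather than significance tests.

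**The case against.** The strongest reply is that this is an omission in a condensed article. The safety section does not say within-arm only or pooled, and layout by arm is commonly left to the full protocol or the statistical analysis plan. That is true of table layout, and an unseen document may tabulate by arm. But the section does more than stay silent. It states which comparison is used for laboratory values and which grouping for AE frequency, and neither is the randomised one.

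Other points against carry weight:

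- Comparing with baseline to look for clinical changes may mean clinical review of individual patients. The percentages in step 3 then do not apply, though the control contrast is still absent.
- Unrelated events are counted as well as associated ones, every AE is listed, and the Adverse events section says that AEs need no causal link and requires SAE reporting whether related or not. A reader might infer that the plan conceals harm. The documents do not support that, because the events remain on record.
- The article does not say who judges relatedness. A reader might infer that the unblinded intervention staff do; this is not stated.
- The AE definition covers events "that occur in test subjects who have received a clinical trial intervention". A reader might infer that control-arm events go unrecorded, but the safety section refers to AEs in the study period without limiting them to one arm.
- The Discussion names usual care as the comparator just after listing safety. That sentence explains the add-on design and is not an analysis rule. The conditional clause on additional analysis specifies no contrast either.

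**Conclusion.** The point holds in limited form. The comparisons named for safety are baseline and judged relation, and the article names no contrast between the randomised arms, although safety is a stated objective and usual care is the trial's comparator. As written, change common to both arms cannot be told apart from a MARS-PD effect, and an all-cause AE excess stays invisible unless the counts are split by arm.

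The size is unknown. Steps 2 and 3 rest on assumed event counts, an assumed drift and a test that the article does not name. A reader might infer that the trial will report false laboratory signals at the rates in step 3, or that no comparison by arm will ever be made. Neither follows from the text. What follows is that the section should name the randomised contrast.

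**What to change.** Amend the Safety evaluation section so that the randomised arms are the main safety contrast:

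1. Report the number of patients with at least one AE, and with at least one SAE, by arm and regardless of judged relation, with the risk difference and 95% CI.
2. Summarise laboratory change and the number of patients with a new clinically relevant abnormality by arm. Give the between-arm difference with 95% CI, adjusted for the baseline value where the measure is continuous.
3. Keep relatedness as a secondary descriptive column, within arm.
4. State that the intervals will be wide at 44 per arm, so that no significant difference is not read as evidence of safety.

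The cost is wording and a few table columns. No patients are added. No data are added either, provided that AEs and follow-up laboratory tests are collected in both arms. That is an assumption here, because the schedule figure is not shown.

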## Materials and methods

### Study design and setting

We aim to assess both the clinical efficacy and cost-effectiveness of the Meridian Activation Remedy System for Parkinson’s Disease (MARS-PD). A single-center, assessor and statistician-blinded, parallel-group randomized controlled trial will be conducted at Daejeon Korean Medicine Hospital of Daejeon University, Daejeon, South Korea between 8^th^ April 2022 and December 2024 (i.e., the recruitment period for this study). The study will encompass 88 patients diagnosed with PD, randomly assigned to either the experimental group (undergoing MARS-PD treatment) or the control group (receiving usual care without additional intervention) in a 1:1 ratio. The experimental group will undergo the MARS-PD intervention twice a week for a duration of 8 weeks, followed by a comprehensive assessment during a 12-week follow-up visit. Conversely, the control group will not receive any additional intervention and will adhere to with their usual care for 8 weeks before participating in a follow-up assessment over the subsequent 12 weeks. This trial design is structured to elucidate the potential benefits of MARS-PD, both in terms of clinical outcomes and cost-effectiveness, providing valuable insights into its impact on PD management, utilizing an equivalence framework (assuming, as our null hypothesis, that the MARS-PD therapy and standard care are equivalent). Additionally, participants in the control group, although not receiving the MARS-PD intervention during the study period, will be eligible for compensation treatment upon successful completion of the trial. This compensation involves acupuncture or MARS-PD intervention sessions (based on the subject’s preference) twice a week, totaling one month. We anticipate that offering this compensatory treatment option may further motivate participants to adhere to the study protocols.

The protocol for this clinical trial adheres to the Standard Protocol Recommendations for Interventional Trials (SPIRIT) guidelines (S1 Appendix) [19]. The clinical trial registry number for the current manuscript can be found in CRIS (Clinical Research Information Service, cris.nih.go.kr, no.: KCT0006646) and in ClinicalTrials.gov’s Protocol Registration and Results (PRS) system (no.: NCT05621772). The SPIRIT schedule of enrollment, interventions, and assessments is shown in Fig 1. The flowchart of this study is shown in Fig 2.

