### Interventions

At a 1:1 ratio, patients will be assigned to either the experimental (MARS-PD intervention) or control (usual care with no additional intervention) groups. Those in the experimental group will undergo the MARS-PD intervention twice a week for 8 a span of weeks, totaling 16 visits. The intervention will be administered by Doctors of Korean Medicine with a minimum of one year of clinical experience in the relevant field, as detailed in the authors’ previous work [16]. In contrast, patients in the control group will adhere to their usual care without any supplementary interventions. Given that the number of steps per day constitutes one of our secondary outcomes, all willing participants, regardless of their group assignment, will receive Samsung Galaxy Fit2 smart band (Samsung Electronics Co., Ltd., Suwon, South Korea), and application-based lifestyle guidance.

During the test period, participants are allowed to engage in personal exercise. However, doctor-prescribed manual therapy, exercise therapy, and rehabilitation treatment specifically tailored for PD are not permitted. This restriction aims to maintain consistency in the intervention conditions and isolate the effects of the MARS-PD being evaluated in the trial.

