### Participant timeline

Among patients who applied to participate in this trial and signed the ICF, the following items will be checked for eligibility assessment: vital signs, the HY scale, the MMSE-K, demographic survey, medical and treatment history, laboratory tests, electrocardiogram, and chest X-ray. Upon random assignment to either the experimental or control group, participants will undergo treatment for a duration of 8 weeks in accordance with their respective group assignments. The MDS-UPDRS Part III, IPAQ, PSQ, PDSS, and economic evaluation questionnaire will be administered four times (0th, 4^th^, 8^th^, and 12^th^ week). TUG, GAITRite, and fNIRS measurements will be taken three times (0^th^, 8^th^, and 12th week). Gut microbiome specimens will be collected and analyzed twice: once at baseline and once at 8^th^ week. Before collecting human specimens, additional consent will be obtained for collection and use of biological specimens.

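### Non-serious adverse event frequencies read by arm would mix harm with opportunity to report, because the MARS-PD arm has about six times as many listed contacts as controls

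*Protocol article*

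**What the plan says.** All references are to the protocol article.

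- **Collection of adverse events (Safety evaluation):** "AE will be gathered through patient-reported symptoms and investigator-made observations".
- **Presentation (Safety evaluation):** "The frequency of AE associated with and unrelated to the intervention will be recorded and presented as descriptive statistics". Further analysis is left open if it proves necessary. No between-arm test is specified.
- **Reporting route (Adverse events):** the principal investigator is to explain possible events to staff, subjects and guardians and "train them to report any phenomena that appear after the intervention". The definition of an adverse event covers those "that occur in test subjects who have received a clinical trial intervention".
- **MARS-PD contact (Study design and setting; Interventions):** "The experimental group will undergo the MARS-PD intervention twice a week for a duration of 8 weeks", "totaling 16 visits".
- **Control contact (Interventions):** "patients in the control group will adhere to their usual care without any supplementary interventions".
- **Shared assessments (Participant timeline):** the motor score, the questionnaires and the "economic evaluation questionnaire will be administered four times", at weeks 0, 4, 8 and 12.
- **Roles (Blinding; Data collection and management):** subjects and intervention staff are unblinded. Intervention staff treat, consult and record the case report forms. Evaluation staff must stay blind. The clinical research coordinator is unblinded, manages schedules and also completes the forms.

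**The concern.** An event that is mild and soon forgotten, such as a stumble, a dizzy spell, soreness or fatigue, is recorded only if the patient reports it or someone notices it. A MARS-PD patient meets treating staff within days of such an event throughout the 8-week treatment period. A control patient's next listed contact may be up to 4 weeks away. With identical true event rates, the arm seen more often would be expected to show more events.

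This matters because the trial names safety among its aims and uses usual care as its comparator. The programme combines needling with exercise that shifts the centre of gravity, in patients who also have such events without it. Readers of a parallel-group trial will set the two columns of an adverse event table side by side even if no test is attached. Under the stated collection method, an excess in the MARS-PD column could reflect harm, better capture or both. Splitting events by relatedness does not remove the problem, because the split is applied after the same unequal capture.

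**Working it through.** **1. The plan's own figure.** 2 sessions per week × 8 weeks = 16, which matches the stated number of visits.

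**2. Listed contacts after baseline.** Controls have weeks 4, 8 and 12, so 3. MARS-PD has 16 sessions plus those assessments. If the week 4 and week 8 assessments fall on session days, the total is 16 + 1 = 17. If all are on separate days, it is 16 + 3 = 19.

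| Count | MARS-PD | Control | Ratio |
|---|---|---|---|
| Baseline to week 12 | 17 to 19 | 3 | 5.7 to 6.3 |
| Treatment period only | 16 to 18 | 2 | 8.0 to 9.0 |
| Baseline visit also counted | 18 to 20 | 4 | 4.5 to 5.0 |
| 75% compliance floor (0.75 × 16 = 12 sessions) | 13 to 15 | 3 | 4.3 to 5.0 |

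None of these counts approaches parity.

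**3. What unequal contact could do (assumed, not from the protocol).** Suppose minor events occur at the same constant rate in both arms over 12 weeks, and each is reported at the next contact if still remembered, with memory fading exponentially with mean *m* weeks. For contacts *d* weeks apart the captured share is (m/d)(1 − e^(−d/m)). Controls have d = 4 throughout. MARS-PD has d = 0.5 for 8 of the 12 weeks and d = 4 for the last 4.

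For m = 4, controls capture 1 − e^(−1) = 0.632. MARS-PD captures (2/3) × 8 × (1 − e^(−0.125)) + (1/3) × 0.632 = 0.837. The ratio is 0.837 / 0.632 = 1.32.

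| Mean recall (weeks) | MARS-PD captured | Control captured | Apparent ratio |
|---|---|---|---|
| 1 | 0.606 | 0.245 | 2.47 |
| 2 | 0.734 | 0.432 | 1.70 |
| 4 | 0.837 | 0.632 | 1.32 |
| 8 | 0.909 | 0.787 | 1.15 |
| perfect | 1.000 | 1.000 | 1.00 |

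**4. The same on a percentage scale (also assumed).** Take a true 30% event rate in both arms, with 90% capture in MARS-PD and 60% in controls. The table would show 0.30 × 0.90 = 27% against 0.30 × 0.60 = 18%, a spurious 9 points. With control capture of 80% or 40%, the gap is 3 or 15 points.

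**5. Direction.** With the same capture, an observed 18% in both arms would correspond to true rates of 0.18 / 0.90 = 20% in MARS-PD and 0.18 / 0.60 = 30% in controls. Similar observed frequencies would then hide a reduction on MARS-PD and not an added harm.

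**The case against.** The strongest reply is that the article condenses a longer protocol. The schedule figure and the protocol appendix are not available here, and either could contain a common adverse event query. That is fair as far as it goes: a common query at shared visits, with session-detected events kept apart, would settle the matter. But asking at every visit would not, because one arm has far more visits. The imbalance follows from the stated visit structure and from pooling everything reported or observed, so it is more than a detail left to another document.

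Other parts of the reply stand and limit the point:

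- A reader might infer that collection is purely spontaneous. The text says only that symptoms are patient-reported, which is compatible with active questioning, and subjects and guardians are trained to report.
- A reader might infer that controls are seen only three times, and only by blinded assessors. The text does not say so. Intervention staff give consultations to subjects without limit to one arm, and the coordinator deals with both arms. The three contacts are those the article lists.
- A reader might infer that a planned between-arm comparison is invalid. None is planned; the frequencies are descriptive and split by relatedness.
- Serious events must reach the principal investigator within 24 hours whatever their cause, and laboratory results are measured. Both are less exposed to recall.
- The illustrated gap is modest against chance. With 44 per arm, 9 points is 0.09 × 44 ≈ 4 patients, and the 95% half-width is 1.96 × √[(0.27 × 0.73 + 0.18 × 0.82) / 44] ≈ 17 points.

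**Conclusion.** The point holds as a design bias in any by-arm reading of non-serious adverse events. The contact imbalance is firm on the listed visits: 17 to 19 against 3, about six to one. The resulting distortion is not known. The apparent ratios of 1.15 to 2.47 and the gaps of 3 to 15 points rest wholly on assumed recall and capture, and they show only that equal true rates could look unequal.

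The likely direction is inflation of apparent MARS-PD harm, or masking of a reduction in events. A reader might go further and conclude that similar frequencies could conceal added harm from the programme. The stated design does not support this, because better capture in the MARS-PD arm works the other way. Nor does it follow that the safety evaluation as a whole fails, since serious events and laboratory changes are less affected.

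The conclusion assumes that the unseen schedule and appendix do not already restrict by-arm tables to a common enquiry at shared visits. It is a change worth making, not an error that undermines the trial.

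**What to change.** At weeks 4, 8 and 12, have the clinical research coordinator, who is already unblinded, ask both arms the same short adverse event question set. It should name falls explicitly and cover the interval since the last assessment. Use these events for any table of non-serious events by arm. List events volunteered or observed at MARS-PD sessions separately, labelled as session-detected, so that none is lost. Keeping the questions with the coordinator also spares the blinded evaluation staff a conversation that could reveal allocation. If the full protocol already contains such a query, it is enough to state there which events enter the by-arm table.

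The cost is a one-page form at three existing visits and one extra table, with no new staff or visits. There are two drawbacks. Recall over up to 4 weeks will miss some minor events in the comparative table. Some reporting bias will also remain, because participants and the coordinator know the allocation and MARS-PD patients may be primed by having discussed events at their sessions.
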